# The EXPRESS Study: Exercise and Protein Effectiveness Supplementation Study supporting autonomy in community dwelling frail older people‐study protocol for a randomized controlled pilot and feasibility study

**DOI:** 10.1186/s40814-017-0156-5

**Published:** 2017-07-06

**Keywords:** Ageing, Frailty, Exercise intervention, Protein supplements

## Abstract

**Background:**

Research has repeatedly demonstrated that exercise has a positive impact on physical function and is beneficial in the treatment of physical frailty. However, an even more effective strategy for managing physical frailty might be the combination of multicomponent exercise with the intake of high-quality protein supplements, but the efficacy remains unclear for older adults who are already pre-frail and frail. The aim is to examine the feasibility of recruiting frail older adults to participate in a trial designed to determine the potential effects of a 6-month exercise and nutrition intervention on physical function. The feasibility objectives will include frail older peoples’ compliance, the safety and tolerability of the trial, the estimation of estimates to aid sample size calculation, and the potential efficacy. Primary outcomes for the main trial will include gait speed, grip strength and physical performance. Secondary outcomes will include frailty status, muscle mass, nutritional intake, physical activity levels, cognitive performance and quality of life.

**Methods/design:**

A randomised, parallel, control pilot and feasibility study will be conducted. All participants will be randomly assigned to either (a) an exercise program + high-quality protein supplement or (b) an exercise program + low-quality protein supplement. Both protein supplements will be matched closely in colour, flavour and packaging so that both the participants and the research staff are blinded. The exercise program will be the same in both groups. Assessments will be conducted at baseline and at 3 and 6 months and include gait speed, grip strength, the Short Physical Performance Battery, Timed Up and Go Test, FRAIL Screen, bioelectrical impedance analyses, 24-h dietary recall, Katz Activities of Daily Living, Lawton Instrumental Activities of Daily Living, the Trail Making Test, Short Form Health Survey-36, and 1 week accelerometer quantification. The data will be analysed using an ANCOVA model.

**Discussion:**

This study is expected to provide much needed insight into the feasibility of recruiting and retaining frail older adults into community-based intervention programs, while providing knowledge relating to the safety, tolerability and benefits of a combined exercise and protein supplement program designed to halt or reverse the transition of physical frailty in the community. If shown to be effective, this strategy could be included in the best practice clinical guidelines for community-dwelling older adults who are pre-frail or frail.

**Trial registration:**

Australian New Zealand Clinical Trials Registry, ACTRN12616000521426

## Background

Globally, the number of people aged 65 years and older is expected to triple over the next 30 years [1, 2]. In Australia, it is estimated that approximately 10 million people will be aged over 65 years by 2050 [3]. A common geriatric syndrome associated with ageing is frailty [4]. Frailty is defined as a “clinically recognisable state of increased vulnerability resulting from age-associated decline in reserve and function” [2] and results in increased morbidity, including disability, loss of independence, increased hospitalizations and reduced quality of life [5, 6]. While frailty is measured using different scales, one of the most commonly used instruments is the Fried Frailty Index [7], which defines frailty according to a physical phenotype consisting purely of physical components. This construct of a physical phenotype is regarded as being distinct from disability or co-morbidity, and hence, the Frailty Index is considered to be highly predictive of future decline in physical health.

Due to the appreciation of the Fried Frailty Index as a relatively easy tool with which to determine whether a person is physically frail, there have been a number of studies that have described the prevalence of this phenotype in different regions around the world. The Survey of Health, Aging and Retirement in Europe (SHARE) surveyed older adults across Europe and Israel using the Fried criteria [7], and the prevalence of frailty was reported to be 17% (range from 5.8% in Switzerland to 27.3% in Spain) [8]. Data from a longitudinal cohort of Australian women using similar frailty criteria reported the same prevalence of pre-frail and frail [9] and, by 2050, this is estimated to represent four million Australians [10]. These data provide impetus for the development of strategies that can be used to either halt or reverse the transition of physical frailty and the manifestation of poor health outcomes. Otherwise, increasing poor health and healthcare costs among this population cannot be mitigated [2, 11].

While physical frailty appears to be reversible when early intervention is provided [7, 9], there remains a lack of consensus regarding the management of older people who are frail or have complex health conditions. Evidence indicates that exercise is critical in managing many of the physiological changes that occur as individuals’ age [4, 12]. Exercise interventions, particularly those that include resistance training, have the potential to prevent, delay and reverse frailty [13]. For example, numerous studies have demonstrated that exercise maintains and restores one or more health parameters including muscle strength, bone integrity, balance and physical function in study populations that include older people who were relatively healthy (i.e. those without a clinical diagnosis) [14] and those classified as frail according to a variety of methods [12, 15]. However, the strength of the evidence from meta-analyses regarding the benefits of exercise for frail older people was limited by the fact that many of the studies reviewed included small and heterogeneous study populations. Few studies have simultaneously measured markers of muscle mass, strength and function; the type of control activity used as the comparator for an exercise intervention has been highly variable; and the compliance to programs has not been well reported. In addition, a study of 151 community-living pre-frail and frail older adults in Singapore showed that improvements in frailty status and a variety of biomarkers of physical frailty were largely comparable for the nutrition, physical, cognitive and combined treatments and all resulted in greater improvement compared with the control, i.e. standard care from health and aged care services in combination with a placebo nutritional supplement. However, while there were no statistically significant differences between the nutrition, physical, cognitive and combined treatments, the improvements in all measured domains where greatest with the physical and combined groups [16]. Accordingly, more studies are needed to identify feasible exercise programs, alone and in combination with other treatments, for community-dwelling pre-frail and frail older adults.

With respect to the nutritional management of pre-frail and frail older people, very few studies have been conducted to determine the effects of protein supplements, either on their own or in combination with exercise. Numerous studies have demonstrated substantial benefits of protein supplementation in combination with resistance exercise in healthy older adults [17, 18]. However, only three studies have been conducted in frail older adults and have yielded conflicting results for the benefits of protein on muscle mass and markers of strength and mobility [19–21]. One study reported increased mobility, but no increase in skeletal muscle mass or strength when consuming additional protein [19], while another showed that protein supplements do not increase the effects of high-intensity functional exercise [21]. Yet another concluded that resistance training, when combined with protein intake, did lead to increased muscle mass compared to resistance training alone [20]. Discrepant findings are likely to be the results of differences in study protocols and participants, with some study samples being too small, while others provided insufficient protein or administered the protein as a single bolus dose, or did not control for differences in background diet.

In addition to the aforementioned limitations of previous research conducted in the ageing field, another major issue are the varied tools used to identify pre-frail and frail older adults. There remains little agreement regarding the diagnostic test accuracy of any of the simple, common diagnostic tests for community-dwelling people. Although interest in the FRAIL Screen is increasing for a number of reasons, this quick, simple screening tool does not require measurements by health professionals and has been validated in various populations across the globe [22–24]. It includes five questions about fatigue, resistance, ambulation, illness and weight loss, representing the phenotypic definition for frailty [7]. The FRAIL Screen can be completed in 15 s. The brevity and simplicity make it useful as a screening tool for implementation in primary care, and it is said to be capable of detecting changes in frailty bidirectionally, and thus may be useful in monitoring for change [22].

Given the incompleteness of our knowledge relating to the efficacy of protein supplements in combination with exercise interventions on physical function in people aged 65 years and older and who are recognised as pre-frail/frail, more information is required. Without a fuller understanding of the effects of a supplement-exercise regimen on frail community-dwelling older adults, it will continue to be difficult, if not impossible, to successfully manage their condition.

## Methods/design

### Aim

The primary aim of this 6-month study is to report on the feasibility of recruiting frail adults aged 65 years and older using the FRAIL screen (e.g. source, speed) and retaining them for the entire 6-month intervention (e.g. compliance, safety, tolerability).

### Feasibility objectives

The feasibility objectives will include the recruitment of pre-frail and frail older people from the community using several recruitment channels, how well pre-frail and frail older people comply with the exercise and nutritional components of the intervention, their completion of the baseline, 3- and 6-month assessments and the safety and tolerability of the intervention. This information will be used to estimate the sample size required for the main trial and the potential efficacy of the main trial.

### Secondary patient-centred objectives

In addition, the study aims to determine the effects of exercise in combination with a protein supplement. The supplement will be either a (a) commercially available high-quality whey protein supplement or (b) a control supplement which is a commercially available lower quality rice protein. Changes in response to exercise in combination with either the low- or high-quality protein supplement will be determined by measurements of the following:Primary outcomes, including gait speed, grip strength and physical performance andSecondary outcomes, including frailty status, muscle mass, quality of life, nutritional intake, cognitive performance and physical activity levels

The primary and secondary outcomes listed above will potentially be used in the main trial after their feasibility is confirmed in this pilot trial.

### Study design

A randomised, parallel, control pilot study will be conducted in a community setting. Participants will be assessed at baseline and at 3 and at 6 months. Participants will be able to withdraw from the study at any time and will have their final assessments completed within 1 week of withdrawal.

### Participants

Participants will be eligible for this study if they are aged 65 years and older, able to converse in English, live in the community and are identified as being pre-frail (i.e. have a score ≥1 but <3 out of 5) or frail (i.e. have a score ≥3 out of 5) using the FRAIL Screen [22], including the following five questions:Are you fatigued?Do you have difficulties walking up one flight of steps?Are you unable to walk at least one block?Do you have more than five illnesses?Have you lost more than 5% of your weight in the past 6 months?

Participants with dementia (i.e. score 5 or less out of 10) as per the Rapid Cognitive Screen [25], severe renal impairment (eGFR ≤30 mmol/L) and those unable to comply with the exercise or nutrition study protocol will be excluded.

### Recruitment

Participants will be recruited through social media (e.g. Facebook), public seminars, local newspapers, radio and television advertising as well as flyers displayed in newsletters and the halls of collaborative aged care services, medical centres, GP practices and the Queen Elizabeth Hospital in Adelaide, South Australia, Australia. The flow of participants through the study will be captured as per the CONSORT statement and as depicted in Fig. 1.

**Fig. 1 Fig1:**
[figure not shown]
EXPRESS Study Consort Flow Diagram

### Randomisation and blinding

The study coordinator will enrol eligible participants into the study and send a participant’s identification number to the study biostatistician who will randomise the participants to one of the two study arms using a stratification system to ensure that an approximately equal numbers of men and women, aged <80 and >80 years, who are pre-frail (score ≥1 but <3 out of 5) and frail (score ≥3 out of 5), are allocated to each arm. The biostatistician will then notify the dietician on the allocated arm prior to the start of the intervention. The participants, as well as the study coordinator and research staff performing the study assessments, will be blinded to the two different types of protein supplements until the end of the trial.

### Exercise intervention

The exercise intervention will be undertaken by all participants who will be supervised by trained exercise physiologists. The exercise regimen includes one centre-based group exercise and two home-based exercise sessions, in addition to walking twice a week. During holiday periods or periods of illness, centre-based exercise can be missed, but participants will be asked to do an additional home-based exercise session if possible. These flexible approaches to the exercise regimen will be recorded.

The exercise prescription is based on the LIFE study, a physical activity intervention for community-dwelling frail older people conducted in the USA [13]. Multi-component exercises incorporating strength, balance, aerobics and flexibility were selected from the LIFE Study and modified for this pilot intervention. Strength exercises will be performed using own body weight, elastic exercise bands and ankle weights. The aerobic modality will be performed using walking exercise. The balance modality will include at least two balance tasks, and the flexibility modality will include the upper and lower extremities. Exercises that are safe and that can be executed in a sitting or safe standing position will be prescribed for the home-based exercise program. Additional exercises that may require more supervision will be included in the centre-based exercise sessions. The intensity of the exercises is based on the LIFE Study design using the Borg Scale [13, 26]. The Borg Scale allows a rating of perceived exertion (RPE) and can be used to monitor and control the intensity of exercise interventions. Strength exercises will be conducted at 15–16 RPE, and walking will be conducted at 12–14 RPE [26].

### Nutrition intervention

A qualified dietician will provide the nutrition prescription and instruct participants on how to prepare and consume the protein supplements and how to record them in the provided compliance diaries. All protein supplements will be provided as a powder in individual 26-g sachets to provide 20 g of protein. The protein powder (i.e. whey or rice protein) will be blended with a powdered flavour (i.e. vanilla) and reconstituted in ~150 ml of water by the participants at home. All drinks will be isocaloric (i.e. both supplying ~90 kcal per 26 g protein sachet) and isonitrogenous (~3.5 g of nitrogen per 26 g protein sachet) and of comparable taste, texture and aroma. The protein powder will be packaged in identical pharmaceutical grade silver foil sachets marked with an A or B to ensure that participants and the study coordinator and research staff performing all study assessments are blinded.

The protein load, source and timing of consumption are based on the recommendations by the PROT-AGE group [27] and the aforementioned meta-analyses [17, 18, 28]. Splitting the total load of protein into two supplements per day is based on evidence that a load of 20 g when combined with multicomponent exercise is sufficient to increase muscle protein synthesis in healthy, non-frail older people. During periods of hospitalisation, research staff will interact with the participant and treating health professionals to encourage, where safe to do so, continuation with the supplementation. Also, it is anticipated that participants will take sachets with them on holidays, thus continuing with supplementation.

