### Compliance and safety

Compliance diaries will be handed out to participants with instructions provided on how to complete them; specifically, they will be asked to record the timing and number of supplements consumed per day. The researchers will check compliance with the supplements and exercise prescription on a weekly basis for the first 2 weeks and then every 2 weeks thereafter if no problems are evident. If the study team identify that a participant’s compliance to the planned number of exercise sessions per fortnight, or the planned number of protein sachets, is less than 70% (i.e. <7 exercise sessions attended or <20 sachets consumed), the research exercise physiologist and dietitian will respectively interview the participant to assess any difficulties and identify strategies that could facilitate compliance.

For participants who have glomerular filtration rates (GFR) of >30 but ≤60 ml/min/1.73 m^2^, the GFR will be retested at 3 and 6 months, and if deterioration is noted (very unlikely), the medical registrar will liaise with the general practitioner and the participant for further assessment and management. Protein supplementation can be safely prescribed up to 1.2 g/kg body weight/day where GFR is >60 [27].

Adverse events (AEs), that is, any untoward medical occurrences (i.e. pain, discomfort, wind, headaches, noticeable difference in body and memory) will be investigated during all visits, whether or not they are related to the study product or physical regimen. The events will be reviewed by the study’s medical registrar and participants will be referred to the research physician as required.

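### One A/B sachet mark for the whole trial makes the blinding fragile, and the abstract claims wider staff blinding than the methods, where the dietician is told the arm

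*Protocol article*

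**What the plan says.** All references are to the protocol article.

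- **Labelling (Nutrition intervention).** Both powders come in "identical pharmaceutical grade silver foil sachets marked with an A or B". The same sentence gives this as the way participants, the study coordinator and the assessing staff are kept blind. The section also matches the drinks on energy, nitrogen and sensory properties.
- **Who learns the allocation (Randomisation and blinding).** "The biostatistician will then notify the dietician on the allocated arm prior to the start of the intervention".
- **Who is blinded, methods (same section).** The list has three entries: the study coordinator, the participants and, thirdly, "research staff performing the study assessments, will be blinded to the two different types of protein supplements until the end of the trial". The dietician is not on it.
- **Who is blinded, abstract (Methods/design).** The supplements are matched "so that both the participants and the research staff are blinded", with no limit on which staff are meant.
- **Dietician's contact at the start (Nutrition intervention).** "A qualified dietician will provide the nutrition prescription and instruct participants on how to prepare and consume the protein supplements", and also on how to fill in the compliance diary.
- **Dietitian's contact later (Compliance and safety).** When fortnightly compliance falls below 70%, "the research exercise physiologist and dietitian will respectively interview the participant to assess any difficulties and identify strategies that could facilitate compliance".
- **Role of compliance (Aim; Feasibility objectives).** Compliance and tolerability are named in the primary aim, and compliance with the nutritional component is a feasibility objective.

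**The concern.** The two-letter mark is the blinding device that the article specifies, so this is a design choice and not a detail left to a fuller document. A mark shared by a whole arm has two weaknesses. It shows who is in the same arm, and it turns one disclosure about one person into a disclosure about everyone whose letter is known. Participants handle the sachets daily at home for six months and meet in centre-based group classes. Both arms follow the same exercise program, and no separation of the classes by arm is described, so comparing letters is easy.

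The second issue is the dietician. Someone in that role is told the arm and then teaches supplement use and diary keeping. A dietitian later helps people with low sachet intake to improve it. If the arm is known in those contacts, the instruction or coaching could differ by arm, and it bears on a primary feasibility measure.

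The outcomes are of a kind that blinding should protect. Gait speed, grip strength and the SPPB depend on effort, while the SF-36, the FRAIL Screen and the dietary recall rest on self-report. They enter a between-arm ANCOVA (Statistical analyses) and are candidates for the main trial (Secondary patient-centred objectives). A weak labelling procedure could therefore be carried forward.

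**Working it through.** The article gives no figure for the quality of blinding, so there is none to reproduce. The check sets the passages side by side, with a little counting.

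**1. What one decoded letter reveals.** Let N be the number randomised (not stated in the article) and K the number whose letter is known to the person concerned, with K at most N. There are two products and two letters, so learning what A stands for also settles B.
- Shared A/B code: arms revealed = K, with an upper bound of N, which is 100% of participants in both arms.
- Code unique to each participant: arms revealed = 1, a fraction 1/N.

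The 100% is a ceiling. It needs the letter's meaning to be learned correctly and every participant's letter to be known, across two study locations. A participant who recognises their own product by taste is unblinded under either scheme. The shared letter is what passes that knowledge on to others.

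**2. Exposure.** Two sachets a day over 14 days is 2 × 14 = 28 per fortnight. Taking six months as 26 weeks (an assumption), this is 13 × 28 = 364 sachets per participant, all with the same letter.

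**3. The interview trigger.**
- Sachets: 0.70 × 28 = 19.6, which agrees with the stated threshold of fewer than 20.
- Exercise: three sessions (one at the centre, two at home) plus two walks a week gives (3 + 2) × 2 = 10 per fortnight, and 0.70 × 10 = 7, which agrees with fewer than 7.

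The trigger is internally consistent and the same in both arms. Knowledge of the arm cannot change who qualifies for an interview on a given diary record. It could change what is said there.

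**4. Abstract against methods.**

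| Role | Abstract | Randomisation and blinding |
|---|---|---|
| Participants | blinded | blinded |
| Study coordinator | blinded (as research staff) | blinded |
| Assessing staff | blinded (as research staff) | blinded |
| Dietician | covered by the unqualified claim | told the allocated arm; not on the blinded list |

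The two differ only in the last row. The methods section does not contradict itself; the abstract is broader than it.

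**5. What the text leaves open.** It does not say whether the dietician is told a letter or a product. It also does not say whether the dietician who is notified is the dietitian who holds the interviews.

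**The case against.** The strongest reply is that the blinding is not shown to have failed anywhere.

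- **A reader might infer that the A/B mark defeats the blinding.** The article does not support that. A letter does not name the product, and the powders are closely matched.
- **A reader might infer that telling the dietician the arm breaks the stated blinding.** Neither the Randomisation and blinding section nor the Nutrition intervention section claims that the dietician is blinded. Only the abstract's wording reaches that far. The allocated arm may also be passed on simply as A or B.
- **A reader might infer that the coordinator can follow the allocation sequence, or that assessors see the letters.** No passage says that either handles sachets. Drinks are made up at home, assessments take place at the study centres, and the allocation goes to the dietician. No block scheme is given, so predictability cannot be shown.
- **A reader might infer that the dietitian runs all the compliance interviews.** The text divides them: the exercise physiologist takes exercise shortfalls and the dietitian takes sachet shortfalls.
- **Flatulence, listed among the example adverse events, might be read as a clue to the arm.** The article does not link it to either product.
- **The stakes are those of a pilot.** The efficacy analysis is described as preliminary, both arms receive protein and exercise, and no between-arm comparison of compliance is stated.

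All of this stands, and it limits the point to fragility and to one inconsistency. It does not answer the labelling issue. The shared letter is the stated device, its failure would spread across the trial, and a pilot is where the procedure for the main trial is tested.

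**Conclusion.** The point holds in a limited form. The trial-wide A/B mark weakens the blinding: one decoded letter reveals up to 100% of allocations, against one participant under unique codes. The abstract's statement about research staff is broader than the methods, because a dietician is told the arm, has direct contact with participants, and is left off the blinded list. Arm-dependent instruction is possible if the dietician knows the product. Arm-dependent coaching of sachet compliance further requires that the interviewing dietitian knows it too. The article settles neither condition.

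No bias can be sized from the document, and unblinding of the assessors remains a risk that is not shown. The conclusion assumes that the group classes mix the two arms, since no separation is described, and that the sachets carry no further participant-specific code. The change is worth making because it is cheap and protects effort-dependent and self-reported outcomes.

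**What to change.** 1. Label the sachets with unique participant or kit numbers in place of A or B. The list linking kit to product is held by the biostatistician or the packer, whoever has no participant contact.
2. Give the dietician only the kit number, and replace the sentence about notifying the arm accordingly. Supplement instruction and sachet-compliance interviews are then done without knowledge of the arm, whether or not one person fills both roles.
3. Align the abstract with the Randomisation and blinding section, so that both name the same blinded roles. Once step 2 is in place, the dietician can be added to that list. If the dietician continues to be told the arm, the abstract should be narrowed to the roles that the methods list, and the methods should state whether a letter or a product name is passed on.

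The cost is label printing, a kit list and slightly more dispensing work, since resupply must go through the list. No extra staff are needed.
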